## Abstract

**Background:**

Critical illness myopathy (CIM) and polyneuropathy (CIP) are a common complication of critical illness. Both cause intensive-care-unit-acquired (ICU-acquired) muscle weakness (ICUAW) which increases morbidity and delays rehabilitation and recovery of activities of daily living such as walking ability. Focused physical rehabilitation of people with ICUAW is, therefore, of great importance at both an individual and a societal level. A recent systematic Cochrane review found no randomised controlled trials (RCT), and thus no supporting evidence, for physical rehabilitation interventions for people with defined CIP and CIM to improve activities of daily living. Therefore, the aim of our study is to compare the effects of an additional physiotherapy programme with systematically augmented levels of mobilisation with additional in-bed cycling (as the parallel group) on walking and other activities of daily living.

**Methods/design:**

We will conduct a prospective, rater-masked RCT of people with ICUAW with a defined diagnosis of CIM and/or CIP in our post-acute hospital. We will randomly assign patients to one of two parallel groups in a 1:1 ratio and will use a concealed allocation. One intervention group will receive, in addition to standard ICU treatment, physiotherapy with systematically augmented levels of mobilisation (five times per week, over 2 weeks; 20 min each session; with a total of 10 additional sessions). The other intervention group will receive, in addition to standard ICU treatment, in-bed cycle sessions (same number, frequency and treatment time as the intervention group).

Standard ICU treatment includes sitting balance exercise, stretching, positioning, and sit-to-stand training, and transfer training to get out of bed, strengthening exercise (in and out of bed), and stepping and assistive standing exercises.

Primary efficacy endpoints will be walking ability (defined as a Functional Ambulation Category (FAC) level of ≥3) and the sum score of the Functional Status Score for the Intensive Care Unit (FSS-ICU) (range 0–22 points) assessed by a blinded tester immediately after 2 weeks of additional therapy.

Secondary outcomes will include assessment of sit-to-stand recovery, overall limb strength (Medical Research Council, MRC) and grip strength, the Physical Function for the Intensive Care Unit Test-Scored (PFIT-S), the EuroQol 5 Dimensions (EQ-5D) questionnaire and the Reintegration to Normal Living Index (RNL-Index) assessed by a blinded tester.

We will measure primary and secondary outcomes with blinded assessors at baseline, immediately after 2 weeks of additional therapy, and at 3 weeks and 6 months and 12 months after the end of the additional therapy intervention.

Based on our sample size calculation 108 patients will be recruited from our post-acute ICU in the next 3 to 4 years.

**Discussion:**

This will be the first RCT comparing the effects of two physical rehabilitation interventions for people with ICUAW due to defined CIP and/or CIM to improve walking and other activities of daily living. The results of this trial will provide robust evidence for physical rehabilitation of people with CIP and/or CIP who often require long-term care.

**Trial registration:**

We registered the study on 6 April 2016 before enrolling the first patient in the trial at the German Clinical Trials Register (www.germanctr.de) with the identifier DRKS00010269. This is the first version of the protocol (FITonICU study protocol).

**Electronic supplementary material:**

The online version of this article (doi:10.1186/s13063-016-1687-4) contains supplementary material, which is available to authorized users.

## Background

Critical illness myopathy (CIM) and polyneuropathy (CIP) are common results of critical illness that frequently occur together. Both cause so-called intensive-care-unit-acquired (ICU-acquired) muscle weakness (ICUAW). Such acquired muscle weakness is characterised by a profound weakness that is greater than normally expected from prolonged bed rest and, therefore, designated as clinically detected weakness in critically ill patients in whom there is no plausible aetiology other than critical illness [1–3]. The weakness of limb muscles significantly limits activities, such as sit-to stand, and assistance in transfers is often required [3–6]. This in turn increases morbidity and delays rehabilitation and recovery of walking [7–9]. Although full recovery has been reported in approximately 50% of people with ICUAW, improvement is related to the severity of the condition, e.g. people with severe weakness may take months to improve, or even remain severely affected [3, 10]. Focused physical rehabilitation of people with ICUAW is, therefore, of great importance. There is practical evidence that physical rehabilitation of patients can be implemented with few adverse effects [1, 11, 12]. Recently, appropriate assessments were developed and descriptions of suitable physical intervention strategies were described in the medical literature [1, 9, 11, 13–16]. Until now many of the described therapies investigated people in the acute stage of ICU treatment [17] with only a few trials considering patients who are so-called chronically critically ill [18] and in the post-acute phase or people in the post-ICU phase [18–20]. There is, therefore, still an urgent need for effective therapy and rehabilitation in the long-term after intensive care, e.g. to improve physical function [20].

### The need for a trial on rehabilitation interventions for people in the post-acute phase with ICUAW

As it seems clear that physical activity may be a promising intervention to address functional challenges for people with ICUAW due to a defined CIP and/or CIM, it is surprising that a recent systematic Cochrane review found no RCTs that examined the effects of physical rehabilitation interventions for people with ICUAW and defined CIP and/or CIM [21]. Several key questions need to be answered. Firstly, is one of two tailored, additional physical interventions more effective in helping people with ICUAW and defined CIP and/or CIM to improve activities of daily living and walking? Secondly, does the range of possible benefits include strength and quality of life, immediately after intervention and on follow-up? Thirdly, what is the optimal and effective physical intervention prescription for people in the post-acute ICU with ICUAW and defined CIP and/or CIM?

### Objective

The objective of the Fitness and mobility training in patients with Intensive Care Unit-acquired muscle weakness (FITonICU) study is, therefore, to describe the effects of an additional physiotherapy programme, with systematically augmented levels of mobilisation, compared with additional in-bed cycling on walking and other activities of daily living. The null hypothesis is that there is no statistically significant difference in the primary outcomes for the applied additional interventions.

We chose these comparators because both mobilisation and in-bed cycling are physical rehabilitation interventions that are commonly used clinically and seem feasible and suitable for these chronically critically ill patients in the post-acute ICU setting. Examples here include (additional) in-bed cycling often being used in critically ill patients on ICU [22] and also in the post-acute phase [18] and a physiotherapy programme with augmented levels of mobilisation is likely to be desirable as mobilisation is often used in the rehabilitation of chronically critically ill patients [3].

We will use a parallel-group randomised controlled trial (RCT) design to investigate the effects of these two different physical rehabilitation interventions for people with ICUAW due to defined CIP and/or CIM.

## Methods/design

### Study design

This is a assessor-blinded, parallel-group, single-centre RCT of people with ICUAW with a defined diagnosis of CIM and/or CIP based on a protocol prepared according to the SPIRIT Statement (www.spirit-statement.org) [23] (see Additional file 1 and for the SPIRIT figure see Fig. 1).

### Screening process

We will enter all patients with the diagnosis of a defined CIP and/or CIM into our screening log. Subsequently, the patient will be screened for eligibility with the inclusion and exclusion criteria as outlined in Table 1 and Fig. 2. We will fully inform eligible patients and/or their caregivers about the study, and we will assign an identification number to the patient. Patients and/or their caregivers are then asked to provide informed consent. In the event that a potential participant does not meet the inclusion criteria, we will not retain identifiable information on that patient. We will report all reasons for exclusion in a flow chart. After providing informed consent we will record all medical and neurological information at baseline in a Case Report Form (Table 2).

**Table 1 Tab1:** Inclusion and exclusion criteria of study

Inclusion criteria
1. Patient is in the post-acute phase and chronically critically ill, defined as more than 21 days ICU of treatment including mechanical ventilation, and at least 14 days more in an existing critical situation with the need for ICU treatment [27, 51, 52]
2. Acquired muscle weakness defined as a Medical Research Council (MRC) sum score of <48 points [1]
3. Defined diagnosis of critical illness myopathy (CIM) and/or polyneuropathy (CIP) confirmed by a neurologist according to published diagnostic criteria for CIP/CIM [24]
4. Older than 18 years of age
5. Richmond Agitation Sedation Scale (RASS) score from −1 to 1 [53]
6. Written informed consent of the patient or their legal guardian has been obtained
Exclusion criteria
1. Patients receiving palliative care
2. Comorbidities of the trunk or the lower limbs interfering with upright posture and walking function (e.g. amputation or fracture of lower limb)
3. Other neuromuscular or neurological disease and/or syndromes causing weakness in patients in the ICU (we will exclude patients with diseases and syndromes causing weakness in patients in the ICU [9], due to Guillain-Barré syndrome, myasthenia gravis, porphyria, Eaton-Lambert syndrome, amyotrophic lateral sclerosis, vasculitic neuropathy, cervical myelopathy and botulism)
4. Severe physical comorbidity before becoming critical ill (e.g. frailty due to neurological conditions)

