### Informed consent

Written informed consent for study participation will be obtained at 1 to 7 days after admission at our department.

Participants will be informed that successful completion of the baseline tests is required prior to randomisation to an intervention group.

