### Outcome measures

Primary efficacy endpoints are walking ability and activities of daily living.

We define our endpoint walking ability with a category of ≥3 on the Functional Ambulation Categories (FAC; 0–5 score range) [25–27]. We use this scale to measure walking ability because in a recent cohort study it has been shown to be a very feasible tool to describe the ability to walk in different settings, such as ICU, post-acute rehabilitation and also at follow-up [26].

We will use the Functional Status Score for the Intensive Care Unit Scored (FSS-ICU; 0–35 score range) [28] to measure elementary activities of daily living. We will use this scale because in a recent cohort study the FSS-ICU was also very feasible, reliable and also predictive (for important aspects of daily living) in different settings and stages such as ICU, post-acute rehabilitation and post-acute care [26].

Our secondary endpoints comprise scales with a comprehensive spectrum of impairments, activities and participation for this population (see Table 2). We will measure the ability to stand up by documenting the ability to stand up from a standardised chair independently (STS) [27]. We will measure muscle strength of the upper (shoulder, elbow and wrist) and lower limb (hip, knee and ankle) using the Medical Research Council (MRC) sum score and calculate and provide a MRC sum score for the upper and also for the lower limbs [1, 27, 29]. We will measure the handgrip strength for both hands using a hand dynamometer (Jamar handgrip dynamometer; Sammons Preston Rolyan, Bolingbrook, IL, USA) [27, 30–32]. We will use the Physical Function for the Intensive Care Unit Test-Scored (PFIT-S) [33] to measure specific ICU impairments. We will assess quality of life using the EQ-5D [34] and measure participation with the Reintegration to Normal Living Index (RNL-Index) [27, 35, 36]. All of these measures are frequently used in research and/or clinical practice dealing with this patient group. Table 2 gives a detailed overview of the variables used at each time point of study and the data collection schedule.

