For the primary endpoint, walking ability, we will analyse the time to regain walking ability (defined as FAC score ≥3) in a time-to-event analysis. We will calculate the probability of regaining walking ability with the Kaplan-Meier (KM, ‘survival analysis’) method [40] and will provide KM plots as appropriate with 95% confidence intervals (CI) including the number of participants at risk at each time. We will report median times until regaining walking ability with 95% CI. The assumptions of KM analysis will be tested with the implemented function of SAS/STAT 9.3 (SAS Institute Inc., Cary, NC, USA). Cox regression analysis will be used to estimate relative hazard rates of the intervention groups [41]. Time to event will be defined as the time difference between study entry (T0) and the date of reaching a FAC score equal to 3, or the possible censoring dates of discharge or treatment refusal or death, respectively. Data will, therefore, be censored appropriately if patients are discharged, refused treatment or died. We will use the log-rank test to test statistically for differences between the KM curves of the intervention groups [42]. We will use a stepwise multivariable Cox regression analysis with a variable selection to also take into account the influence of all dependent variables (PROC PHREG; best subset analysis; SAS 9.3, SAS Institute Inc., Cary, NC, USA) [41, 43]. The following dependent-variable categories will be analysed for their association with walking ability:Demographic variables at baseline (such as age and sex)All clinical variables at baseline (such as muscle strength, PFIT-S; Table 2) andMedical characteristics at baseline (such as diagnosis and duration of primary illness)

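### The walking analysis has no at-risk condition at T0, and its event date is tied to FAC equal to 3 although the endpoint is FAC ≥3

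*Protocol article*

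**What the plan says.** Screening process sends the reader to two places: patients are "screened for eligibility with the inclusion and exclusion criteria as outlined in Table 1 and Fig. 2". Table 1 lists six inclusion and four exclusion criteria. The weakness criterion is "Acquired muscle weakness defined as a Medical Research Council (MRC) sum score of <48 points". The one criterion that mentions walking is an exclusion for "Comorbidities of the trunk or the lower limbs interfering with upright posture and walking function", which removes patients with another cause of impaired walking, not patients who already walk. FAC is scored at T0 (Table 2). Informed consent states that "successful completion of the baseline tests is required prior to randomisation to an intervention group", so the tests must be done, but no FAC result is required.

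Outcome measures states: "We define our endpoint walking ability with a category of ≥3 on the Functional Ambulation Categories". Statistical methods repeats FAC ≥3 and analyses time to regaining it with Kaplan-Meier, log-rank and Cox methods. The time variable, however, is "the time difference between study entry (T0) and the date of reaching a FAC score equal to 3". Censoring is listed for discharge, treatment refusal and death. Intention to treat is the primary analysis. Nothing shown says how a patient at FAC ≥3 at T0 is handled.

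**The concern.** A time-to-event analysis of regaining a function needs patients who lack it at time zero. The criteria shown do not secure this. The MRC sum score covers the upper as well as the lower limbs (Outcome measures), so a score below 48 does not by itself establish inability to walk. Two problems follow.

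- **No at-risk condition.** A patient at FAC 3 at T0 has, on the natural reading, a time to event of zero. Such events carry no information on treatment. They drop both Kaplan-Meier curves at the start, shorten the reported medians and pull the arms together.
- **An event date that does not match the endpoint.** A patient at FAC 4 or 5 at T0, or one who later moves from below 3 straight to 4, meets FAC ≥3 but never literally has a score of 3. The endpoint definition and the date rule give that patient different status.

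At stake are the precision and meaning of one of the two primary endpoints. The FSS-ICU endpoint is not touched.

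**Working it through.** **Inputs (Sample size section).** FSS-ICU difference 6, SD 10, alpha 5% (taken as two-sided), power 80%, 45 per arm before dropout; walking recovery 0.6 versus 0.4. The share q already at FAC ≥3 at T0 is not in the documents; 0–20% is an assumed range.

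**The plan's own figure.** n per arm = 2(1.96 + 0.84)² × (10/6)² ≈ 44 by normal approximation, and 44.6, so 45, by the exact t test. The stated 45 is reproduced. It rests on FSS-ICU and does not depend on q.

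**Walking as a proportion.** If baseline walkers count as successes in both arms, each rate p becomes p′ = q + (1 − q)p, so the difference becomes 0.20 × (1 − q). Power = Φ{[d√n − 1.96√(2p̄(1 − p̄))] / √(p₁(1 − p₁) + p₂(1 − p₂))}, with n = 45.
- q = 0: (0.20 × 6.708 − 1.96 × 0.707)/0.693 = −0.064, power 47%.
- q = 10%: rates 0.64 and 0.46; (0.18 × 6.708 − 1.96 × 0.704)/0.692 = −0.248, power 40%.

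**Walking by log-rank, the planned test.** The hazard ratio implied by the two rates is ln(0.4)/ln(0.6) = 1.79, with ln HR = 0.584. Expected events are 45 × (0.6 + 0.4) = 45. Power = Φ(√45/2 × 0.584 − 1.96) = 50%.
- *Baseline walkers left out of the risk set:* events fall to 45(1 − q) = 40.5 at q = 10%, power 46%.
- *Baseline walkers counted at time zero:* the signal is 40.5 × 0.584/4 = 5.92. Its variance is 40.5/4 = 10.1, plus 9 × 0.25 × 81/89 = 2.05 from nine tied events among 90 patients. Then z = 5.92/√12.17 = 1.70 and power is Φ(1.70 − 1.96) ≈ 40%.

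| Assumed share q | Rates | Two-proportion power | Log-rank, left out | Log-rank, counted at time zero |
|---|---|---|---|---|
| 0 | 0.600 v 0.400 | 47% | 50% | 50% |
| 2% | 0.608 v 0.412 | 46% | 49% | 48% |
| 5% | 0.620 v 0.430 | 44% | 48% | 44% |
| 10% | 0.640 v 0.460 | 40% | 46% | 40% |
| 20% | 0.680 v 0.520 | 34% | 42% | 32% |

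The direction is certain for any q above zero; the size depends on q. Leaving these patients out of the risk set recovers part of the loss (46% rather than 40% at q = 10%), but not all of it, because fewer patients are at risk.

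**The case against.** The strongest case against is that these patients may hardly exist. Entry requires "more than 21 days ICU of treatment including mechanical ventilation, and at least 14 days more in an existing critical situation", together with MRC below 48 and confirmed CIP or CIM. Consent is taken within a week of admission, in post-acute ICUs and weaning units. The plan expects FSS-ICU means of only 22 and 16 out of 35 after two weeks of therapy. At a 2% share the loss is one or two points of power. The words regain and recovery show that non-walkers were in mind, and handling of patients already at the endpoint could sit in a fuller document.

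Much of this stands. The share is probably small, and the 20% row is an outer bound, not an expectation. Some baseline walkers remain plausible all the same: the plan assumes 40–60% recover walking, and the MOBILITY exercises extend to walking 10 m and climbing stairs. The mismatch between FAC equal to 3 and FAC ≥3 is in the text whatever the share.

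A reader might infer three stronger things that the documents do not support.

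- *That the protocol orders baseline walkers to be counted at time zero.* It does not; that is the natural reading of a rule that is silent on them.
- *That eligibility is shown to contain no FAC limit anywhere.* Fig. 2 is cited alongside Table 1 and cannot be seen. It is captioned as a design flow chart, so a further criterion there is possible but not indicated.
- *That FAC 0–2 must be added to the inclusion criteria.* Recruitment began in April 2016, so this would be a mid-trial amendment, and it would remove patients who still inform FSS-ICU.

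Nor should the low walking power be put down to this point: it is about 47–50% with no baseline walkers at all.

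**Conclusion.** The point holds as a defect in how the walking analysis is specified, not as an eligibility failure. The criteria shown admit patients at FAC ≥3, the clock starts at T0 with no at-risk condition, and the event date rule does not match the endpoint. Followed as written, such patients either enter as uninformative events or have undefined status.

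The practical effect is probably small. The power losses rest on an assumed share, on the planning rates of 0.6 and 0.4 applying to true non-walkers, on equal shares in both arms, and, for the log-rank figures, on a hazard ratio derived from those rates under proportional hazards. The FSS-ICU sample size of 45 per arm stands.

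**What to change.** In Statistical methods:

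1. Define the risk set for the walking analysis as all randomised patients with FAC 0–2 at T0. The baseline tests are completed before randomisation, so this restriction keeps the randomised comparison intact; apply it blind to arm.
2. Define the event as the first documented FAC of 3 or more, replacing the wording that ties it to a score of exactly 3. Table 2 already provides for daily FAC documentation.
3. Report by arm the number of patients at FAC ≥3 at T0.
4. Keep those patients in the FSS-ICU analysis.

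The cost is a few lines of text and no new data. The downside is that the walking set may be slightly smaller than the full intention-to-treat set (40.5 rather than 45 per arm if the share were 10%), which should be stated in the report. An eligibility amendment is optional and not needed.

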**Fig. 2 Fig2:**
[figure not shown]
Flow chart of the Fitness and mobility training in patients with Intensive Care Unit-acquired muscle weakness (FITonICU) study design

**Table 2 Tab2:** Overview of enrolment, interventions and assessments of the Fitness and mobility training in patients with Intensive Care Unit-acquired muscle weakness (FITonICU) study

Time point	Enrolment pretreatment	Allocation	Baseline (T0)	2 weeks post treatment (T1)	Daily documentation	3-week follow-up (FU1)	6- and 12-month follow-up (FU2–3)
Enrolment							
Eligibility screening	x						
Informed consent	x						
Allocation	x	x					
Interventions							
Physiotherapy			x	x	x	x	
Occupational			x	x	x	x	
therapy							
Other therapies (e.g. groups)			x	x	x	x	
Additional			x	x			
interventions			x	x			
Primary outcome							
FAC score			x	x	x	x	x
FSS-ICU			x	x		x	x
Secondary outcomes							
STS			x	x	x	x	x
MRC sum score			x	x		x	
Grip strength			x	x		x	
PFIT-S			x	x			
EQ-5D						x	x
RNL-Index						x	x

*FU* follow-up, *T* time point, *FAC* Functional Ambulation Categories, *FSS*-*ICU* Functional Status Score for the Intensive Care Unit Scored, *STS* ability to stand up from a chair independently, *MRC sum score* Medical Research Council (sum score of muscle strength of the upper (shoulder, elbow and wrist) and the lower limb (hip, knee and ankle)), *PFIT*-*S* Physical Function for the Intensive Care Unit Test-Scored, *EQ*-*5D* EuroQol 5 dimensions questionnaire, *RNL*-*Index* Reintegration to Normal Living Index

Two of the investigators will conduct all baseline assessments (see Table 2 for details). Those study assessors will not be involved in treating patients or with administration of the intervention and will remain fully blinded to the patient’s group allocation throughout the whole trial.

